“Adverse events,” as defined by the World Health Organization [19], will be recorded from medical records, direct observation during classes, and by participants’ self-reporting to document the safety of the intervention. The event may or may not be related to the intervention but may occur while the individual is participating in the intervention phase of the trial. Adverse events will be categorized as minor or serious, related or unrelated, and expected or unexpected. A minor adverse event is defined as an incident that occurs during the intervention but results in no injury or minor injury requiring no or minor medical intervention. A serious adverse event is defined as an incident that occurs during the intervention, resulting in death, serious injury, or hospitalization (eg, injurious fall resulting in fracture). Serious adverse events will also be recorded for the usual care group. In addition, adverse events will be reported and graded using the Common Terminology Criteria for Adverse Events Version 4 [20]. The consequences of a serious adverse event in the control group (eg, hospitalization and emergency-department admission) will be captured by the health service utilization questionnaire and medical record audit. Reasons for nonparticipation in an exercise session or noncompletion of the program will also be recorded (eg, pain, fatigue, and feeling unwell).

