### Participant Safety and Ethical Considerations

The quality of the water will be routinely observed and recorded. Until medically cleared, children with open wounds, central lines, or symptoms of skin infections will not be allowed to participate in aquatherapy. Before each session, a pediatric oncologist will check all participants for symptoms of fever or active infections. For emotional support during the first sessions, parents or other caregivers may be present. The research ethics board will be notified of all adverse events, mild or major. Before participating, families will be briefed on any possible dangers and asked to sign a form providing informed consent and assent. Periodically, a data safety monitoring team will examine events and make necessary protocol adjustments.

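### As written, the plan collects minor adverse events in the aquatherapy arm but names only serious ones for the comparator, which it mislabels, and its event definitions leave out weeks 4 to 12

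*Protocol article*

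**What the plan says.** Everything here is in the protocol article.

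- **Sources and purpose** (Study Outcomes, adverse event paragraph after Table 2). Events come from medical records, "direct observation during classes, and by participants’ self-reporting to document the safety of the intervention". No arm is named.
- **Period.** An event need not be related to the intervention, but it "may occur while the individual is participating in the intervention phase of the trial".
- **Minor event.** "A minor adverse event is defined as an incident that occurs during the intervention but results in no injury or minor injury", needing at most minor medical attention.
- **Serious event.** "A serious adverse event is defined as an incident that occurs during the intervention, resulting in death, serious injury, or hospitalization".
- **Comparator.** "Serious adverse events will also be recorded for the usual care group". The consequences of a serious event in the control group come from a health service questionnaire and an audit of medical records.
- **Grading.** Adverse events are graded with CTCAE version 4; no arm is named.
- **Reporting** (Participant Safety and Ethical Considerations). "The research ethics board will be notified of all adverse events, mild or major". A data safety monitoring team reviews events periodically and may adjust the protocol.
- **What the comparator is** (Table 1). Conventional physiotherapy, supervised, 45 minutes, 5 sessions a week for 4 weeks, with strengthening, resistance and balance work.
- **Follow-up** (Study Design; Study Outcomes). Assessments at weeks 0, 4 and 12.

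**The concern.** A sentence saying that serious events are *also* recorded in one arm is needed only if the capture just described did not already cover that arm, and it extends serious events alone. Staff who follow it would have no instruction to record minor events in the comparator.

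The label adds to the problem. Usual care suggests an arm without study sessions, where nobody is present to observe. The actual comparator is supervised exercise, which can cause minor events of its own in front of a therapist who could record them.

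The definitions raise a second problem. Tying both event types to the intervention leaves the period after week 4 outside adverse event collection, although the children are assessed to week 12.

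At stake is any description of harms by arm, and the monitoring team's decisions. A difference created by collection could be taken for a hazard of aquatherapy. Minor events that were never recorded cannot be recovered by a later analysis.

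**Working it through.** **1. The texts side by side**

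| Item | Aquatherapy arm | Comparator |
|---|---|---|
| Minor events | Records, observation, self-report | None stated specifically |
| Serious events | Same sources | Stated; consequences from questionnaire and record audit |
| Name used in the adverse event paragraph | The intervention | Usual care group, control group |
| Supervised sessions (Table 1) | 3 a week | 5 a week |
| Notice to ethics board | All events, mild or major (no arm named) | All events, mild or major (no arm named) |

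The last row requires notification of minor events from the comparator, but no sentence expressly has them collected there.

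**2. The window**

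The intervention lasts 4 weeks and assessment runs to week 12. If *during the intervention* means the phase, 12 − 4 = 8 weeks lie outside the definition. If it means the sessions, the time between sessions is lost as well.

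On the session reading, time at risk also differs between the arms:

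- Aquatherapy by Table 1: 3 × 4 = 12 sessions; 12 × 45 = 540 minutes.
- Comparator by Table 1: 5 × 4 = 20 sessions; 20 × 45 = 900 minutes.
- Aquatherapy, if given on top of the full conventional programme, as the Experimental Group section words it: 12 + 20 = 32 sessions; 32 × 45 = 1440 minutes.

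So the comparison is 540 or 1440 minutes against 900, unequal either way. The two descriptions of the experimental arm themselves need reconciling.

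**3. Illustration of size**

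The plan's only relevant figure is the group size. Its own formula gives 2 × (1.96 + 1.64)² / (1.12 / 1.09)² = 24.55, plus 1.96² / 2 = 1.92, so 26.47, rounded up to 27 per group. That reproduces. It serves here only as the denominator.

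Assumptions that are not in the documents: the same true risk p of at least one minor event in both arms, full capture under aquatherapy, and a captured fraction c in the comparator. The expected difference in recorded proportions is then p × (1 − c), all of it artefact. At p = 30%, the expected counts are 27 × 0.30 = 8.1 against 0 when c = 0, 8.1 against 4.05 when c = 0.5, and no difference when c = 1.

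For the extreme case c = 0, with e events against 0, the two-sided Fisher exact P is 2 × C(27, e) / C(54, e):

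- e = 5: 2 × 80,730 / 3,162,510 = 0.051
- e = 6: 2 × 296,010 / 25,827,165 = 0.023
- e = 8: 2 × 2,220,075 / 1,040,465,790 = 0.0043

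Six recorded events are therefore the fewest that give P < .05. The chance of six or more among 27 children is:

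| Assumed true risk in both arms | Chance of a spurious P < .05 |
|---|---|
| 10% | 5% |
| 20% | 46% |
| 30% | 86% |
| 50% | over 99% |

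**The case against.** Several stronger readings are tempting, and the document does not support them.

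- **Minor events are expressly excluded in the comparator.** The text never says *only*. The opening sentence on sources and the grading sentence name no arm, and the ethics board is to hear of every event. Equal capture may have been intended. This makes serious-only capture an inference, though the natural one. It does not supply an instruction to collect minor events in the comparator, and it leaves two sections that do not agree.
- **Events between sessions do not count.** The sentence before the definitions refers to the intervention phase and admits unrelated events, and medical records would be an odd source for in-session incidents alone. The phase reading is the likelier one. On it, the window limits scope equally in both arms, unless the so-called usual care group is held to have no intervention.
- **The two arms use different detection sources for serious events.** Medical records are in the general list too, and the questionnaire and audit concern the consequences of a serious event. This contrast is weak.
- **Infection is the main hazard and would be missed.** The safety section lists water quality, wounds, central lines, skin infection and fever checks but ranks none of them, and all participants are checked for fever or infection before each session. The Abstract also has readmissions and emergency presentations recorded, though not as adverse events and with no stated window.
- **The P values show a false finding in waiting.** They assume zero capture in the comparator, which is the disputed point, and event rates that the protocol does not give. The Statistical Analysis section plans no between-arm safety test, and at a 10% risk the chance of a spurious result is only about 5%.

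It is also fair to say that an intervention-phase window is a declared choice, and that nothing here affects the primary endpoint or the sample size.

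**Conclusion.** The point holds as a defect in how adverse event collection is specified. Followed as written, the plan would most naturally yield minor events from one arm only, so harms could not be compared by arm and aquatherapy would probably look worse on minor events. The comparator is misnamed, and the paragraph does not fit the reporting rule in the next section. The event definitions are ambiguous between sessions and phase, and on either reading they omit weeks 4 to 12.

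The size is unknown. It depends on the true minor-event risk and on how much is captured in the comparator. The artefact runs from none with equal capture to the full event rate with no capture, which is about 8 children in 27 at an assumed 30%. A reader might infer a bias that is stated outright in the plan, or a planned test that would go wrong; the document shows neither. What makes the correction worthwhile is that it is cheap before data collection and that missing minor events cannot be restored afterwards.

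**What to change.** Amend the adverse event paragraph under Study Outcomes, before recruitment or as early in it as possible:

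1. State that all adverse events, serious and non-serious, are collected in both arms with the same definitions, sources and CTCAE grading.
2. Give one time window for both arms, preferably from randomisation to the last visit. If the shorter window is kept, say that it means the 4-week phase and that later events are not collected.
3. Define a serious event by its outcome within that window, and not by its occurring during the intervention. Record relatedness as a separate field.
4. Replace the usual care label with conventional physiotherapy group.
5. Reconcile the paragraph with the rule in Participant Safety and Ethical Considerations that all events go to the ethics board.

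The cost is one common event form and more entries to record and report, including those from weeks 4 to 12. Therapists already see the comparator children five times a week during the intervention, and the week 12 assessment offers a contact for the rest.

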**Methods:**

We will conduct a parallel, single-blinded (participant-blinded), randomized controlled trial with embedded quantitative analysis. In total, 54 survivors of ALL undergoing chemotherapy will be recruited from the Acharya Vinoba Bhave Rural Hospital in Sawangi (Meghe), Wardha, Maharashtra, India. The experimental group will attend a 4-week, thrice-weekly, 45-minute aquatherapy session focusing on exercise-based rehabilitation. The comparison group will receive conventional physiotherapy including standardized exercises. Assessments will be completed at weeks 0 (baseline), 4 (postintervention), and 12 (follow-up). The primary outcome related to motor function will be measured using the timed up and go test and the Pediatric Balance Scale at week 4. Secondary outcomes will include psychosocial well-being measured with the Hospital Anxiety and Depression Scale and functional abilities measured with the Functional Independence Measure for Children (WeeFIM). Health service data, including length of stay in the hospital, hospital readmissions, and emergency department presentations, will be recorded. Semistructured interviews will be completed within an interpretive description framework to explore participant descriptions. The primary outcome will be analyzed using linear mixed effects models.

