## Introduction

Acute lymphoblastic leukemia (ALL) is one of the most common cancers affecting children, with about 64,200 cases reported worldwide. In India, the highest incidence occurs among children aged 2–5 years, with rates of approximately 101.4 cases per million boys and 62.3 cases per million girls [1]. The availability of more advanced therapeutic agents, enhanced supportive care, therapy stratification, and regimen modification in recent times has led to a cure rate of more than 80% and an overall survival probability of 80% to 90%. As a result, awareness about therapy-related morbidity has increased because of the longer survival rates [1].

Acute chemotherapy comprises 2 phases: the induction phase and the consolidation phase. The primary goal of the induction phase is remission. Intense chemotherapy is used during this phase, which typically lasts 4 weeks, to destroy as many leukemia cells as possible. After a successful induction therapy session, patients are moved into the consolidation phase, sometimes referred to as intensification. This phase is aimed at eradicating any leukemia cells that could have remained unaffected during the induction phase. Additional chemotherapy regimens that are different from those used in induction are part of the consolidation phase, which usually lasts many months. This is the most intense phase, requiring a prolonged hospital stay. Children with ALL are considerably less active during the acute stage, usually presenting with deficits in fatigue and activity tolerance [2,3]. They may also exhibit motor deficits as a side effect of the chemotherapy drugs, which include anthracyclines and vincristine. While anthracycline-induced cardiotoxicity reduces aerobic capacity, vincristine-induced neuropathy impairs peripheral sensory and motor function [4,5]. Chemotherapeutic drugs such as vincristine have an adverse effect on balance, which may occur through diverse mechanisms such as by decreasing muscular strength and flexibility or producing cognitive impairment [1]. When used on children with ALL, these drugs can result in self-imposed or medically prescribed activity restrictions, which would lead to routinely engaging in lesser physical activity [1,6].

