### Study Outcomes

Participants will be assessed at weeks 0, 4, and 12. The primary end point is immediately after the intervention (week 4). Physical activity, balance, and psychosocial well-being will be assessed at weeks 0 and 4. Primary and secondary outcomes are as outlined in Table 2.

**Table 2 table2:** Primary and secondary outcomes, measures, and time points of the intervention.

Outcomes	Measures or sources	Definitions	Time points
Primary outcome: balance	Pediatric Balance Scale [16]; reliability 0.97	This 14-item scale is simple to administer, does not require any specialized equipment. Performance can be measured both quantitatively and qualitatively using a 0 to 4 grading system.	Wk 0; wk 4
Functional mobility	Timed up and go test [1,17]; reliability (ICC>0.80)	The test evaluates functional mobility and balance by timing how long it takes a participant to get up from a seated posture, walk 3 min, turn around, go back, and sit down. <10 s—typical mobility; 10-14 s—independent walking but modest motor deficits. >20 s—severe restrictions with higher risk of fall; 15-20 s—intermediate mobility issues, requiring some assistance	Wk 0; wk 4
Secondary outcome: motor function	Functional Independence Measure for Children (WeeFIM) [18,19]	A popular instrument for evaluating the functional capacities of individuals undergoing rehabilitation, the functional independence measure focuses on independence in everyday activities. Each of the 18 items in the FIM is scored on a scale of 1–7, with higher scores indicative of greater independence. The items are separated into motor and cognitive categories. Development and rehabilitation requirements of individuals can be inferred from their overall score, which ranges from 18 (total reliance) to 126 (full independence).	Wk 0; wk 4
Psychosocial well-being	Hospital Anxiety and Depression Scale (supplementary file [18])	It is a 14-item questionnaire used in hospital settings to measure sadness and anxiety. Each of the two subscales (depression and anxiety) has 7 items and is scored between 0 and 3, with a maximum score of 21 per subscale; 0-7 (normal), 8-10 (mild), 11-15 (moderate), and 16-21 (severe) are the interpretations for the scores. The HADS^a^ is a useful instrument for early detection and monitoring of mental health issues in individuals receiving therapy because a score above 8 suggests substantial symptoms.	Wk 0; wk 4

^a^HADS: Hospital Anxiety and Depression Scale.

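### The Abstract promises health service data for the trial, but the only collection route in the Methods is stated for serious adverse events in the control group, so no common method for both arms is described

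*Protocol article*

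**What the plan says.** **Abstract, Methods.** The secondary outcomes are named first: "Secondary outcomes will include psychosocial well-being measured with the Hospital Anxiety and Depression Scale and functional abilities", the latter by WeeFIM. A separate sentence follows: "Health service data, including length of stay in the hospital, hospital readmissions, and emergency department presentations, will be recorded". It names no arm, source or time point.

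**Study Outcomes.** The text states that "Primary and secondary outcomes are as outlined in Table 2". Table 2 has four measures (Pediatric Balance Scale, timed up and go, WeeFIM, Hospital Anxiety and Depression Scale), all at weeks 0 and 4. It has no health service row.

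**Study Outcomes, adverse event paragraph.** Adverse events in general "will be recorded from medical records, direct observation during classes, and by participants’ self-reporting to document the safety of the intervention". The definition reads: "A serious adverse event is defined as an incident that occurs during the intervention, resulting in death, serious injury, or hospitalization". Then: "Serious adverse events will also be recorded for the usual care group". Finally, the results of such an event "in the control group (eg, hospitalization and emergency-department admission) will be captured by the health service utilization questionnaire and medical record audit". This is the only mention of the questionnaire and the audit in the article.

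**Statistical Analysis.** The variables named are the clinical scales. No health service variable appears.

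**The concern.** The Abstract's promise covers the whole trial. The one sentence in the Methods that says how such data are obtained names one arm and one trigger. A site team following it literally would give the questionnaire and run the audit for control children who had a serious event, and would have no written instruction to do the same for aquatherapy children.

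At stake is the comparability of any hospitalization, emergency visit or serious adverse event counts that are later set side by side. If one arm is asked with a questionnaire and audited while the other relies on routine adverse event recording, a difference in counts may reflect how the events were found and not the therapy. The overlap with safety reporting makes this more than tidiness, because hospitalization is part of the definition of a serious adverse event.

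The wording also fits this design poorly. It speaks of a usual care group, as though the comparator had little contact with the trial team. Table 1 gives that group supervised 45-minute physiotherapy sessions five times a week for 4 weeks. An extra retrieval route for the control arm would make sense if its children were not otherwise seen, but here they are seen more often than the three weekly aquatherapy sessions require.

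**Working it through.** The article gives no figure to reproduce on this point, so the check is a comparison of passages.

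| Question | Abstract | Table 2 | Adverse event paragraph | Statistical Analysis |
|---|---|---|---|---|
| Which health service items? | Length of stay, readmissions, emergency presentations | None | Hospitalization and emergency admission, as examples | None |
| Which arm? | Not restricted | – | Control group, for questionnaire and audit | – |
| What trigger? | None stated | – | A serious adverse event | – |
| What source? | None stated | – | Questionnaire and audit (control); records, observation and self-report (adverse events in general) | – |
| When? | None stated | – | Adverse events are tied to the intervention period | – |

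1. **Is there one stated method for both arms?** No. The unrestricted statement has no source, and the statement with a questionnaire and audit is worded for the control group.

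2. **Do the general adverse event sources close the gap?** In part. Records and self-report are not limited by arm, so some capture is described for aquatherapy children. But a serious adverse event must occur during the intervention, which lasts 4 weeks, whereas Study Design sets a follow-up assessment at week 12. That route does not reach weeks 4 to 12. It also gives no source for length of stay, or for an admission that did not arise from an incident.

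3. **Can the distortion be sized?** If the true proportion of children with an event is p in both arms, and the shares captured are c₁ (control) and c₂ (aquatherapy), the apparent difference is p × (c₁ − c₂). The article gives none of p, c₁ or c₂. The sign is also open. A questionnaire and audit used only in control would raise c₁, while counting only events linked to a serious adverse event in control, against all use in aquatherapy, would lower it.

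4. **What scale is at issue?** Sample Size Estimation gives 27 per group. One child counted under one rule and missed under the other shifts that arm's proportion by 1/27 = 0.037, or 3.7 percentage points. Two children shift it by 2/27 = 7.4 points. This shows how sensitive the counts are and does not estimate a bias.

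**The case against.** The strongest reply is that the sentence on the control group describes safety capture and is not the collection plan for health service data. It refers to the questionnaire as though it were already in general use. On that reading, a trial-wide questionnaire and audit simply also pick up serious events in control children. The article is condensed, and the schedule may be in the full protocol. This stands as a possible reading and keeps the point small. It does not remove it, because the article does more than leave detail out: it states a rule and attaches it to one arm.

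Several stronger readings are tempting, and the article does not support them.

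- **That the questionnaire and audit are used only in control.** The text never says so, and never says they are withheld from the aquatherapy arm.
- **That the arms cannot be compared.** This does not follow. Records and self-report cover both arms, serious events are recorded in both, and recruitment is from one hospital.
- **That health service use is a trial outcome.** The Abstract says the data will be recorded, after it has listed the secondary outcomes. The aims, Table 2 and the analysis section do not include them, and no between-arm test of them is planned.
- **That a bias of a given size can be quoted.** Any such figure would rest wholly on assumed event and capture rates, with even the direction unknown.
- **That failing to separate planned from unplanned admissions is an error.** The Introduction says of consolidation, "This is the most intense phase, requiring a prolonged hospital stay", so scheduled admissions are likely. But event definitions are detail an article may leave to the full protocol, and scheduled admissions would occur in both randomized arms.

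**Conclusion.** The concern holds in a limited form. The Abstract's health service data have no matching entry in Table 2 or the analysis section, and the one collection route described is worded for serious events in the control group. No common method for both arms is described, so any between-arm description of hospitalizations, emergency visits or serious adverse events is open to differential ascertainment. Its size and direction cannot be derived from the article.

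Severity is minor: the Pediatric Balance Scale, timed up and go, WeeFIM and anxiety and depression results are untouched, as are the sample size and every stated analysis. The conclusion assumes that the sites work from the wording shown. If the full protocol already applies the questionnaire and audit to both arms, only the published sentence needs correcting.

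**What to change.** In the adverse event paragraph of Study Outcomes, change the reference to the control group so that it covers both groups. State that the same questionnaire and the same record audit are applied to every child at the same planned visits (for example weeks 4 and 12), whether or not a serious adverse event has occurred.

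If that is not intended, remove health service data from the Abstract and draw no between-arm conclusion from whatever is recorded. Listing admissions scheduled for chemotherapy separately would make the counts easier to read, but is optional.

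The cost is a wording change. The instrument, the audit and the visits already exist. If aquatherapy children are not already given the questionnaire, it would be used in up to 27 more children. The change is easiest before recruitment starts.
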